### Patient allocation

After patients have provided baseline assessments and been checked for eligibility they will be asked for their informed consent to take part in the trial. The method of fixation will be allocated using a secure, centralized, NHS N3 computer database (CREST) via a secure web-browser page by a member of the research team. Randomization will be conducted on a 1:1 basis, stratified by centre. The allocation sequence will be based on an algorithm written by the trial statistician and the CREST developer.

Stratification by centre will help to ensure that any clustering effect related to the centre itself will be equally distributed in the trial arms.

### Blinding

Trial participants, hand therapists conducting the Total Active Motion assessment, composite flexion and wrist movements, and research nurses administering the Disabilities of Arm, Shoulder and Hand Outcome Measure, Patient Evaluation Measure, visual analogue scales and EuroQol five dimensions questionnaire will be blinded to the method of intervention.

The operating surgeon, clinician assessing for complications at follow-up visits and individuals assessing the patient radiographs will not be blinded.

Blinding will be achieved by only allowing the permissible individuals to have access to the method of fixation information, the operation record and radiographs of the participant.

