### Objectives

The primary objective is to compare union rates between unicortical and bicortical screw and plate fixation of diaphyseal metacarpal fractures. Patients will be assessed for fracture union 6 months after their fracture fixation using radiographs, assessed by an independent musculoskeletal radiologist and a senior consultant hand surgeon; a third consultant hand surgeon will be consulted for verification in cases where there is disagreement.

The secondary objectives are to compare the implant failure rate, complication rate and functional outcomes between the two groups. Functional outcome measures will include scores on the Disabilities of the Arm, Shoulder and Hand Outcome Measure, the Patient Evaluation Measure, the EuroQol five dimensions questionnaire, and a visual analogue scale for pain, function, movement and satisfaction, as well as a range-of-motion assessment of the affected wrist and finger.

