#### Fixation method

A 2.0 mm straight plate will be applied through an incision over the dorsal aspect of the hand. The details of the surgical approach will be left to the discretion of the surgeon. A minimum of two screws will be used on each side of the fracture to hold the fracture. For patients assigned to unicortical fixation, only the near cortex will be drilled and nonlocking screws only engaging the near cortex will be used to hold the reduction. For patients assigned to bicortical fixation, both the near and far cortices will be drilled and nonlocking screws will engage both cortices. The same type of plate and screws will be used for both fixation methods.

Patients will be blinded to their treatment regardless of the type of anaesthetic used. For patients undergoing a regional anaesthetic block, a visual drape will be used and audio-visual distraction will be available.

The method of closure will be left to the discretion of the surgeon. Both patient groups will have a bulky dressing following the operation; the dressing will not inhibit the movement of the fingers and will allow early controlled range-of-movement exercises.

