#### Primary outcome measure

The primary outcome measure for this study will be assessment of fracture union at 6 months.

Three-view (anteroposterior, lateral, and oblique views) radiographs of the hand at admission, 6 weeks and 6 months will be independently evaluated by two observers (a consultant musculoskeletal radiologist and an orthopaedic hand surgeon). In situations where there is conflict, a third senior hand surgeon will be asked to assess the radiographs and cast a deciding vote. The initial fracture assessment will include fracture displacement and angulation measured on a standard Picture Archiving and Communication System workstation (Agfa Impax 6, Agfa Healthcare), and pre-existing osteoarthritis in the hand. Union assessment on post-operative radiographs will be based on visibility of fracture lucency on each view. Fracture union will be defined as ‘united’ if trabeculae are seen crossing sclerosis at the fracture, ‘partially united’ if part of a lucent fracture line is still seen, ‘probably united’ if there is no clear gap but the fracture cannot be defined as ‘united’ based on the criteria, and ‘not united’ if fracture lucency can be clearly seen. If the fracture is partially united, the ratio of width of bridging trabeculae to the entire fracture length will also be recorded as an objective measure of degree of fracture union. Assessment of surgical plate and screws will be recorded for lucency at the metal bone interface, migration or breakage.

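### The readers who decide the primary outcome are left unblinded without a stated reason, and nothing in the article keeps them from the allocation or the operation record

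*Protocol article*

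**What the plan says.** All references are to the protocol article.

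- **Primary outcome measure:** "The primary outcome measure for this study will be assessment of fracture union at 6 months". It is read from anteroposterior, lateral and oblique films by a radiologist and a hand surgeon working separately, and a further hand surgeon decides if they disagree. The basis is visual: "Union assessment on post-operative radiographs will be based on visibility of fracture lucency on each view". There are four grades, from united to not united, with partially united and probably united between them. The same section also asks for the plate and screws to be assessed for lucency, migration and breakage.
- **Objectives:** union is "assessed by an independent musculoskeletal radiologist and a senior consultant hand surgeon", again with a third surgeon if needed.
- **Blinding:** patients, hand therapists and the nurses giving questionnaires are blinded. The operating surgeon and the clinician assessing complications are not, and "individuals assessing the patient radiographs will not be blinded". Blinding is to be kept by "only allowing the permissible individuals to have access to the method of fixation information, the operation record and radiographs" of the participant. The section does not name the permissible individuals.
- **Participant timeline:** follow-up clinicians are unblinded so that they can check radiographs for complications. No reason is given for the union readers.
- **Fixation method:** in the unicortical arm "only the near cortex will be drilled and nonlocking screws only engaging the near cortex will be used to hold the reduction", while in the bicortical arm the screws engage both cortices.

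**The concern.** Blinding protects the functional and questionnaire outcomes, which are secondary, but not the outcome on which the trial's conclusion rests. Union here is a judgement. Probably united, for instance, means that no clear gap is seen but the criteria for united are not met. On such films, knowing the arm, who operated or how the patient is doing can tip the grade.

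The tilt could go either way. The Discussion presents unicortical fixation as easier and quicker, with potentially fewer complications, and as a possible future standard. A reader who shares that view may grade doubtful unicortical films as united. The Background calls bicortical fixation the standard practice, so a sceptical reader may do the reverse. The first tilt makes a false claim of non-inferiority more likely, and the second costs power.

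**Working it through.** **Is the exposure stated or inferred?** That the readers are unblinded is stated in Blinding. That they may see the allocation and operation record is an inference: they are named as unblinded just before access is reserved for unnamed permissible individuals. The article therefore supports saying that they are not barred from the records, and no more.

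**Does the stated reason cover them?** The reason in Participant timeline is the detection of complications by follow-up clinicians. Blinding lists the complication clinician and the radiograph assessors separately, so that reason does not extend to the union readers.

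**The plan's own figure first.** Sample size assumes 8 % non-union in each arm, a margin of 10 points, 80 % power and 126 per group. As an equivalence calculation (two one-sided tests at 0.05):

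n = 2 × 0.08 × 0.92 × (1.645 + 1.282)² / 0.10² ≈ 126.06 per group

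This agrees with 126, and 252 / 0.80 = 315. The present point does not depend on that figure; only 126 per arm and the margin are carried forward.

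**Illustration of bias towards unicortical fixation.** Non-union is treated as a yes/no outcome. The true rates are set at the margin, 18 % unicortical (8 % + 10 points) and 8 % bicortical. A share b of unicortical non-unions ends up graded united after adjudication. The documents give no value for b, so a range is shown.

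- Observed rates: p_U = 0.18 × (1 − b), p_B = 0.08
- SE = √[(p_U(1 − p_U) + p_B(1 − p_B)) / 126]
- Chance of declaring non-inferiority = Φ[(0.10 − (p_U − p_B)) / SE − z], with z = 1.960 (one-sided 0.025) or 1.645 (one-sided 0.05)

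For b = 10 %: p_U = 0.162, SE = √[(0.1358 + 0.0736) / 126] = 0.0408, and Φ(0.018 / 0.0408 − 1.960) = Φ(−1.52), about 6.5 %.

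| b (assumed) | p_U | False non-inferiority, 0.025 | False non-inferiority, 0.05 |
|---|---|---|---|
| 0 | 18.0 % | 2.5 % | 5.0 % |
| 5 % | 17.1 % | 4.1 % | 7.7 % |
| 10 % | 16.2 % | 6.5 % | 11.4 % |
| 20 % | 14.4 % | 14.7 % | 23.1 % |

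**What the adjudication rule does.** If each of three readers independently upgraded 20 % of unicortical non-unions, the final grade would be upgraded in 0.20² + 2 × 0.20 × 0.80 × 0.20 = 0.04 + 0.064 = 10.4 % of them. The row for b = 10 % thus corresponds to about 20 % per reader if their errors are independent. If the readers share the same leaning, the rule dampens less.

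**Leniency in both arms.** With 20 % of non-unions upgraded in each arm, the observed difference is 0.144 − 0.064 = 8.0 points, SE = √[(0.1233 + 0.0599) / 126] = 0.0381, and Φ(0.020 / 0.0381 − 1.960) = Φ(−1.44), about 7.6 % at one-sided 0.025.

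**Bias against unicortical fixation.** With 8 % true non-union in both arms, over-calling unicortical non-union by 1, 2 or 3 points lowers non-inferiority power at one-sided 0.025 from 83.3 % to 72.6 %, 60.3 % or 47.5 %.

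**The case against.** The strongest objection is that the films themselves reveal the arm. The arms differ in whether the screws reach the far cortex, the readers see lateral and oblique views, and they must inspect the hardware. Withholding paperwork may leave much of the unblinding in place. This stands: the remedy is partial, and nothing in the documents shows how much bias it would remove. It does not answer why readers should also be free to see the operation record, surgeon or clinical course, none of which is needed to grade lucency.

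A second objection is that safeguards exist: a radiologist described as independent, two specialties reading separately and a third vote. These limit the influence of any one reader. But reading separately is not reading masked, and nothing expressly keeps a surgeon-reader from grading a patient he or she treated. Fuller rules on reader assignment may sit in the full protocol, so the weight rests on the stated lack of blinding and not on that silence.

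A reader might go further and infer that the readers are handed the allocation and operation records. The Blinding section does not say so. A reader might also infer that the exposure could be removed at no cost; the documents say nothing on cost, and export and handling of images take work.

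Nor would an analysis restricted to the anteroposterior view be a sound way round the visible screws. The article does not say that a separate union grade is recorded for each view. The plate is placed through a dorsal incision and may obscure the fracture line in that projection, and the added misclassification would tend to pull the arms together.

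**Conclusion.** The concern holds in a limited form. The article expressly leaves the assessors of the primary outcome unblinded, gives a reason that fits only other clinicians, and does not bar the union readers from the allocation or operation record. This is a stated design rule and not a detail lost in condensing the protocol.

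The size of any bias is unknown, and its direction could favour either arm. The figure of 2.5 % rising to about 6.5 % rests on true rates of 18 % and 8 %, 126 evaluable patients per arm, a yes/no outcome and an assumed 10 % of unicortical non-unions finally read as united. It shows that modest misreading matters at this sample size; it does not estimate what will happen. The point deserves a change to the plan because part of the exposure is avoidable, though not all of it.

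**What to change.** Amend the Blinding section, with a matching line under Primary outcome measure, so that:

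1. the same readers grade union on de-identified films in random order, without allocation, operation record, surgeon identity or clinical notes;
2. no reader, including the third surgeon, grades a patient whom they operated on or followed up;
3. the union grade is recorded before the plate-and-screw assessment;
4. the trial report states that masking was only partial, because screw length may show on lateral and oblique views.

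The change needs no extra readers or films and leaves the sample size as it is. It costs some work in exporting and ordering images and assigning readers, and residual unblinding from visible screws remains. Clinicians checking for complications can stay unblinded as planned.

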### Data management

All trial data will be stored on the secure NHS N3 server based at the host hospital, i.e. University Hospitals Birmingham. The study team from the host hospital, from the University Hospitals Birmingham NHS Trust, or relevant regulatory authorities, where it is relevant to their taking part in this research, may have access to participants’ data. Such information will be treated as strictly confidential, and will be handled in accordance with the provisions of the UK Data Protection Act 1998.

### Statistical analysis

Baseline data (e.g. age and sex) will be summarized to check comparability between treatment arms, and to highlight any characteristic differences between those individuals in the study. Standard statistical summaries (e.g. medians and quartiles or means and standard deviations, dependent on the distribution of the outcome) and graphical plots will be presented for the primary and secondary outcome measures.

Differences between treatment groups will be assessed on an intention-to-treat basis. Tests will be two-sided and considered to provide evidence for a significant difference if *P* < 0.05 (5 % significance level). Estimates of treatment effects will be presented with 95 % confidence intervals.

The temporal patterns of any complications will be presented graphically and, if appropriate, a time-to-event analysis (Kaplan–Meier survival analysis) will be used to assess the overall risk and risks within individual classes of complications (e.g. implant failure).

Missing data are not expected to be a problem for this study. If the degree of data loss is relatively low, the primary analysis will be based on complete cases only, with analysis of imputed datasets used to assess the sensitivity of the analysis to the missing data. If the level of missing data is higher than expected, missing data will be imputed using the multiple imputation facilities available in R (http://www.r-project.org/).

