## Methods/Design

### Design

This is a prospective, pragmatic, multi-centre, randomized controlled non-inferiority trial. This study was approved by the NHS Research and Ethics Committee (no 14/WM/1212, 12 December 2014) and the UK National Health Service (NHS) Coordinated System for Gaining NHS Permission (National Institutes for Health Research Clinical Research Network study ID 18642).

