### Recruitment, ethics and consent

Patients will be recruited from NHS clinics and accident and emergency departments of at least three teaching hospitals in England, which each have a specialist hand surgery unit. A member of the surgical team will introduce the trial to eligible patients; if patients would like more information, they will be given the trial patient information documentation and a member of the research team will be informed. Patients will usually have 24 hours to consider participation but will have a minimum of 60 min in exceptional circumstances (e.g. trauma theatre space available on the day of presentation). Written consent will be obtained by a member of the research team, which will include consent for the randomized data of the study to be published in scientific peer-reviewed journals. Baseline pre-operative assessments will be obtained following consent. Randomization will take place immediately before surgery.

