### Trial interventions

All of the hospitals involved in this trial currently use both of the methods of fixation and all of the surgeons involved will be familiar with both techniques. Operative fixation of fractures will take place under an axillary brachial plexus regional anaesthetic block or a general anaesthetic block, according to the anaesthetist’s preference. Patients will be randomized immediately pre-operatively to the method of fixation using a trial management database program entitled ‘Clinical Research Tool’ (CREST), designed by University Hospitals Birmingham computer and information technology developers and the trial statistician. Patients will be blinded to their treatment throughout the trial duration.

In this trial, the details of the surgery will be left to the discretion of the surgeon to ensure that the results of the trial maintain external validity.

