### Outcome measures

Patient characteristics and baseline (pre-injury) functional status will be collected after consent to take part in the trial has been obtained. Structured information regarding other injuries that may affect outcome, e.g. previous wrist injury, will be collected. All patients will be included in the analysis. Assessments will be performed at 2 weeks, 6 weeks and 6 months following patients’ operation. Results will be collected by a blinded hand therapist.

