### Sample size

Published data indicate a non-union rate of 8 % when plates and screws are used to fix metacarpal fractures [14]. Assuming this value in each group, a total of 252 patients (126 patients per group) would have an 80 % chance of demonstrating equivalence, with a margin of 10 %, of the failure rates of unicortical and bicortical fixation with 95 % confidence. From previous local audits of hand trauma studies, a drop-out rate of 20 % can be expected. Assuming a drop-out rate of 20 %, we would need 315 patients in total.

The level of 10 % is based on the limited data available currently on what differences could be expected after treating metacarpal fractures with bicortical fixation, compared with unicortical fixation.

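### Intention-to-treat is the only comparison basis named for a non-inferiority trial; if unicortical patients are converted to bicortical screws, a claim about the technique as received becomes easier

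*Protocol article*

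**What the plan says.** The Design section states "This is a prospective, pragmatic, multi-centre, randomized controlled non-inferiority trial", and the Discussion repeats that design. On the comparison of groups, the Statistical analysis section says "Differences between treatment groups will be assessed on an intention-to-treat basis", and the Outcome measures section adds "All patients will be included in the analysis". No per-protocol, as-treated or other adherence-based analysis is named. The one sensitivity analysis concerns missing outcomes: if data loss is low, "the primary analysis will be based on complete cases only", with imputed data as the check. It does not touch the technique received.

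On delivery of the intervention, the Recruitment section says "Randomization will take place immediately before surgery", and the Trial interventions section says "the details of the surgery will be left to the discretion of the surgeon". The Blinding section lists the operating surgeon among those not blinded. Against this, the Fixation method section is specific for the unicortical arm: only the near cortex is drilled, and the screws engage only that cortex. The article gives no conversion rate and does not say how a patient treated otherwise than allocated would enter a second analysis.

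**The concern.** In a superiority trial, mixing of treatments pulls the arms together and makes a positive finding harder, so intention-to-treat is the cautious choice. In a non-inferiority trial the same mixing moves the estimate towards zero and makes the claim easier. A unicortical patient who ends up with bicortical screws still counts as unicortical but may carry bicortical risk.

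The setting makes this possible. Allocation precedes the operation, the surgeon is unblinded and familiar with both techniques, and the same type of plate and screws serves both arms. The Discussion says a favourable result may make unicortical fixation the standard method. If conversions were frequent, that conclusion could rest partly on mixed techniques, with nothing in the stated analysis to show it.

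**Working it through.** **Inputs from the Sample size section.** "Published data indicate a non-union rate of 8 % when plates and screws are used to fix metacarpal fractures", assumed in each group; "would have an 80 % chance of demonstrating equivalence, with a margin of 10" per cent; 126 per group, 252 in total; 20 % drop-out; 315 to recruit.

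**The plan's own figure.** Equivalence by two one-sided tests at 5 % each, unpooled variance:

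n per arm = 2p(1−p)(z₀.₉₅ + z₀.₉₀)² / margin² = 2 × 0.08 × 0.92 × (1.645 + 1.282)² / 0.10² = 126.06.

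This gives 126 per arm and 252 in total, and 252 / (1 − 0.20) = 315. Both stated figures reproduce.

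**Assumptions for the dilution check (none of these is in the article).**
- True failure is 18 % unicortical and 8 % bicortical, so the difference sits exactly at the 10-point margin.
- A share c of the unicortical arm is converted and then has the 8 % risk.
- Conversion is unrelated to prognosis.
- Non-inferiority is claimed when the upper limit of the two-sided 95 % Wald interval is below 10 points.

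**Formula.** The unicortical rate under intention-to-treat is 0.18(1 − c) + 0.08c = 0.18 − 0.10c, so the difference is 0.10 − 0.10c. The claim probability is found by enumerating both binomial distributions at 126 per arm. The normal approximation is Φ(0.10c / SE − 1.96), with SE = √[(0.08 × 0.92 + p(1 − p)) / 126] and p = 0.18 − 0.10c.

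Example at c = 0.10: p = 0.17, SE = 0.0413, 0.010 / 0.0413 − 1.96 = −1.72, so Φ = 4.3 %.

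| Converted | Difference (points) | Normal approximation | Exact enumeration |
|---|---|---|---|
| 0 % | 10.0 | 2.5 % | 2.7 % |
| 2 % | 9.8 | 2.8 % | 3.1 % |
| 5 % | 9.5 | 3.3 % | 3.6 % |
| 10 % | 9.0 | 4.3 % | 4.7 % |
| 20 % | 8.0 | 7.1 % | 7.6 % |

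At the one-sided 5 % level that underlies the 252, the exact rates are 5.5 % with no conversion, 6.9 % at 5 %, 8.7 % at 10 % and 13.3 % at 20 %.

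**Power cost of a per-protocol set.** With 8 % failure in both arms and conversions dropped from the unicortical arm, exact non-inferiority power (95 % limit) is 83 % with none dropped, about 81 % at 10 % (113 v 126 patients) and 78 % at 20 % (101 v 126).

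**If conversion is selective.** For illustration, suppose 10 % of the unicortical arm are poor-hold cases with 40 % failure if left unicortical, the arm averaging 18 % overall. The other 90 % then fail at (0.18 − 0.10 × 0.40) / 0.90 = 15.6 %.
- Poor-hold cases convert and fail at 30 %: the intention-to-treat rate is 0.14 + 0.03 = 17.0 %, false-claim rate 4.7 %. Per-protocol (15.6 %, 113 v 126) gives 9.5 %.
- Conversion restores 8 % risk: the intention-to-treat rate is 0.14 + 0.008 = 14.8 %, false-claim rate 13.1 %. Per-protocol stays at 9.5 %.

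Which set is nearer the truth therefore depends on facts that the article does not give.

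**The case against.** The strongest reply has four parts.

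First, conversions are not documented. The Fixation method section prescribes which cortices are engaged, so the general discretion over surgical detail need not extend to that choice. A reader might infer from the discretion and the timing of allocation that conversions will occur and that the error rate is in fact inflated. The article supports neither inference; it shows only that conversion is possible. This stands, and the result is conditional.

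Second, the trial is pragmatic. For the policy of allocating patients to unicortical fixation, 10 % conversion makes the true difference 9 points, which is inside the margin, and declaring non-inferiority would be correct. This stands too. The inflation concerns the technique as received, and a reader who concludes that intention-to-treat is the wrong analysis goes too far.

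Third, the statistical analysis plan is not shown and may name a second set. The point therefore cannot be that the trial has no per-protocol analysis. But the article is not silent on the matter: it names one basis, says all patients are analysed, and pairs this with two-sided tests for a difference, as in a superiority trial. That stated choice is open to comment.

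Fourth, a per-protocol set may be the worse one. The selective example confirms it (9.5 % against 4.7 %). This limits what the remedy can promise, but it does not favour relying on intention-to-treat alone, since the other selective case runs the opposite way (13.1 % against 9.5 %).

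**Conclusion.** The point holds in a conditional form. The article names intention-to-treat as the only basis for comparing groups in a non-inferiority trial. If unicortical patients are converted, the difference under that basis shrinks and a claim about the technique as received becomes easier. Under the stated assumptions (difference at the margin, 126 per arm, bicortical risk after conversion, no selection, 95 % upper-limit rule), the false-claim rate goes from 2.7 % to 3.6 % at 5 % conversion, 4.7 % at 10 % and 7.6 % at 20 %. That is minor at 5 % or below and material from about 10 %. Intention-to-treat remains valid for the pragmatic question. It would be wrong to read these figures as the trial's actual error rate, because neither the conversion rate nor the claim rule comes from the article.

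**What to change.** Keep the intention-to-treat analysis. Add a per-protocol analysis of union at 6 months, restricted to eligible patients in whom every screw followed the allocated method, as taken from the operation record. Define the set before outcomes are examined. Claim non-inferiority only if both analyses support it against the 10-point margin, and write down the interval rule used. Report the number of conversions in each arm, so that readers can judge how much dilution was possible.

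The cost is one further analysis and a recorded item on the screws used. Per-protocol power falls from 83 % to about 81 % at 10 % conversion and 78 % at 20 %; requiring both sets to agree costs somewhat more. The per-protocol set is not protected by randomization and can be biased in either direction if conversion is selective, for example when poor-hold cases drop out of it. Agreement of the two sets is a safeguard and should be reported as such; it does not restore the nominal error rate.

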## Discussion

The SUBMIT trial is, to our knowledge, the first clinical trial to assess the efficacy of unicortical screw and plate fixation in patients with metacarpal fractures. Unicortical plate and screw fixation of metacarpal fractures is a less technically demanding and quicker procedure with, theoretically, less soft tissue disruption and potentially fewer complications.

Published studies have not proven a superiority of one fixation method over the other in cadaveric models. This study has been designed as a non-inferiority trial. We believe that should this study demonstrate equivalence between unicortical and bicortical fixation, unicortical fixation may become the standard method of fixing metacarpal fractures requiring surgery in the future.

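### The analysis section's only decision rule is a two-sided test for a difference; the promised 95 % confidence interval is never compared with the 10-point margin on which the trial was sized

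*Protocol article*

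**What the plan says.** Four places in the protocol article bear on this.

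- **Design:** "This is a prospective, pragmatic, multi-centre, randomized controlled non-inferiority trial". The Discussion repeats it: "This study has been designed as a non-inferiority trial".
- **Sample size:** "Published data indicate a non-union rate of 8 % when plates and screws are used to fix metacarpal fractures". With that rate in each group, 126 patients per group (252 in total) are said to give 80 % power to show equivalence of failure rates within 10 %, with 95 % confidence. A 20 % drop-out allowance brings the total to 315.
- **Statistical analysis:** differences between groups are assessed by intention to treat. The rule is "Tests will be two-sided and considered to provide evidence for a significant difference if" P is below 0.05. Treatment effects will be shown with 95 % confidence intervals. The section does not mention the margin, non-inferiority or equivalence, and it makes no exception for the primary outcome.
- **Discussion:** the change of practice is tied to equivalence: "should this study demonstrate equivalence between unicortical and bicortical fixation, unicortical fixation may become the standard method".

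**The concern.** The design and the sample size pose one question: is unicortical fixation worse by less than 10 points? The analysis rule tests another: do the two rates differ at all? A P value below 0.05 shows a difference in one direction or the other. A P value above 0.05 shows only that no difference was detected, and a trial that is small, noisy or short of follow-up produces it more easily. Neither result rules out a deficit of 10 points.

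The primary conclusion is at stake, and with it the change in standard practice that the Discussion foresees. The P value and the interval can point different ways, and the plan does not say which of them decides.

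**Working it through.** **Inputs.** From Sample size: non-union p = 0.08 in both groups, margin d = 0.10 (taken as an absolute risk difference), n = 126 per group, power 80 %, drop-out 20 %. From Statistical analysis: two-sided 5 % test, 95 % intervals.

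**1. Reproducing the planned sample size.** The variance term is 2p(1 − p) = 2 × 0.08 × 0.92 = 0.1472.

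| Hypothesis | Formula | n per group |
|---|---|---|
| Equivalence, two one-sided 5 % tests (90 % CI) | 0.1472 × (1.645 + 1.282)² / 0.10² | 126.06 |
| Equivalence, two one-sided 2.5 % tests (95 % CI) | 0.1472 × (1.960 + 1.282)² / 0.10² | 154.7, so 155 |
| Non-inferiority, one-sided 2.5 % (95 % CI) | 0.1472 × (1.960 + 0.842)² / 0.10² | 115.5, so 116 |
| Non-inferiority, one-sided 5 % (90 % CI) | 0.1472 × (1.645 + 0.842)² / 0.10² | 91.0, so 92 |
| Two-sided difference test, 8 % v 18 % | standard two-proportion formula | 177 |

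Of these, only equivalence by two one-sided 5 % tests gives 126. The drop-out step is exact: 252 / 0.80 = 315. The sample size therefore rests on a margin-based hypothesis, and the analysis rule does not use the margin.

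**2. How far apart the two rules are.** All pairs of outcomes were enumerated from exact binomial probabilities at 126 per group. The difference test is the pooled two-sided z test. The margin rule requires the upper Newcombe 95 % limit for unicortical minus bicortical to be below +10 points.

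| True non-union, bicortical v unicortical | Difference test non-significant | Margin rule met |
|---|---|---|
| 8 % v 8 % | 95.1 % | 79.6 % |
| 8 % v 15 % | 58.5 % | 11.0 % |
| 8 % v 18 % (at the margin) | 33.7 % | 2.5 % |

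With a Wald interval, the margin rule is met 2.7 % of the time at 8 % v 18 % and 83.1 % at 8 % v 8 %.

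**3. A single data set.** Take 10/126 bicortical and 18/126 unicortical non-unions.

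- Difference: 8/126 = 6.3 points.
- Test: the pooled rate is 28/252 = 0.111, so the standard error is √(0.111 × 0.889 × 2/126) = 0.0396. Then z = 0.0635/0.0396 = 1.60 and P = 0.11.
- Wald 95 % CI: the unpooled standard error is √(0.0794 × 0.9206/126 + 0.1429 × 0.8571/126) = 0.0394. The interval is 6.3 ± 1.96 × 3.94, or −1.4 to +14.1 points.

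No significant difference is found, yet a deficit of up to 14 points is not excluded.

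**4. Power of a margin rule at 126 per group, 8 % in both groups.**

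| Rule | Normal approximation | Exact, Newcombe |
|---|---|---|
| Non-inferiority, 95 % CI | 83 % | 80 % |
| Equivalence, 90 % CI | 80 % | 77 % |
| Equivalence, 95 % CI | 67 % | 59 % |

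**The case against.** Two stronger readings are tempting, and the document supports neither.

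- **That practice would change on a non-significant P value.** The Statistical analysis section says what P below 0.05 means. It nowhere says that P above 0.05 shows non-inferiority or equivalence. The Discussion makes the change conditional on showing equivalence. The 34 % and 59 % are therefore error rates of a likely misreading, not of a stated rule.
- **That the trial cannot answer its question.** The margin is given and 95 % intervals are promised, so the data will allow a valid conclusion. The failing lies in the stated rule.

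It can also be said that this is a condensed article, that the missing link is one sentence which the full protocol or the analysis plan may contain, and that the P < 0.05 sentence is generic text meant for secondary outcomes. This does not remove the point. The section did not leave the rule open: it stated one, without excepting the primary outcome, and that rule does not fit the design. An analysis plan with the right rule would have to override the article, not just add detail to it.

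A last objection stands in full. A repair that assumes one-sided non-inferiority at 2.5 % passes over the equivalence wording in Sample size and Discussion, and 126 per group reproduces only as equivalence with one-sided 5 % tests. That has to be settled in the same edit.

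**Conclusion.** The point holds in this form: the one decision rule in the analysis section tests for a difference, the design needs a comparison with a margin, and the section does not link its confidence interval to that margin. It should be corrected because it governs the primary conclusion.

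The size is conditional. If non-significance were taken to mean no worse, that conclusion would be reached 34 % of the time with unicortical non-union exactly at the margin, against 2.5 % under the interval rule.

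The figures assume 126 evaluable patients per group, 8 % bicortical non-union, an absolute 10-point margin, and a two-category union outcome.

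**What to change.** In Statistical analysis:

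1. **Primary rule.** Estimate the risk difference in non-union, unicortical minus bicortical, with a two-sided 95 % confidence interval (score or Newcombe). Conclude non-inferiority only if the upper limit is below +10 percentage points.
2. **Difference test.** Keep the P < 0.05 rule for secondary outcomes, and for superiority on the primary outcome only after non-inferiority is shown.
3. **Hypothesis and interval level.** Reconcile non-inferiority (Design, Discussion) with equivalence (Sample size, Discussion) and state the matching interval level. If equivalence is meant, both limits must lie within ±10 points, and the level matters. By normal approximation, 126 per group gives 80 % power with a 90 % interval and 67 % with a 95 % interval, for which 155 per group would be needed to reach 80 %.
4. **Binary outcome.** State which of the four union grades in the Primary outcome measure section count as non-union, since a risk difference needs two categories.

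The cost is a change of wording. The non-inferiority rule needs no extra patients: power at 126 per group is about 80 % (Newcombe) to 83 % (Wald). Only equivalence with a 95 % interval would call for a larger trial.
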